### Sample size

2.6

In our preliminary study, the change of subjective symptoms in the treatment group was 7.21 ± 4.36 and 4.35 ± 3.15 in the control group. Taking α as 0.05, β as 0.2 with a 2-sided test, and considering a dropout of 20%, 72 patients will be needed totally.

### Statistical methods

2.7

SPSS 21.0 (SPSS Inc, Chicago, IL) will be used for data analysis. The measurement data will be expressed as mean ± standard deviation. Considering the normality and homogeneity, *t* test, or nonparametric test will be applied for the changes between the 2 groups. Repeated measurement analysis of variance or generalized linear model will be applied for repeated measurement data. *P* < .05 will be considered statistically significant.

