### Outcome measures

2.5

The primary outcomes are the changes of subjective symptoms of fatigue, anorexia, halitosis, nausea, itching, and edema evaluated at week 0, week 4, and week 8. The corresponding score will be 2, 4, and 6, respectively, according to the degree of mild, moderate, and severe. The secondary outcomes are patient global assessment scale, serum creatinine, cystatin C, and estimated glomerular filtration rate at week 0 and 8. The patients will be followed for another 4 weeks after the treatment. The incidence and types of related adverse events, vital sign measurements, and physical examinations will also be recorded.

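### Section 2.7 names no baseline adjustment and does not fix one primary analysis, so precision from the week-0 score is lost and the primary estimand can change with the data

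*Protocol article*

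**What the plan says.** Section 2.5 of the protocol article makes the change in six symptoms the primary outcome, assessed at weeks 0, 4 and 8, and grades each symptom: "The corresponding score will be 2, 4, and 6, respectively, according to the degree of mild, moderate, and severe". The secondary outcomes are a patient global assessment scale and "serum creatinine, cystatin C, and estimated glomerular filtration rate at week 0 and 8". Every one of these outcomes therefore has a baseline value.

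Section 2.6 sizes the trial on unadjusted mean change: "the change of subjective symptoms in the treatment group was 7.21 ± 4.36 and 4.35 ± 3.15 in the control group". The other inputs are "Taking α as 0.05, β as 0.2 with a 2-sided test", and "considering a dropout of 20%, 72 patients will be needed totally".

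Section 2.7 gives two analysis statements. In the first, the data's normality and homogeneity decide whether a t test or "nonparametric test will be applied for the changes between the 2 groups". In the second, repeated data are analysed by repeated-measures ANOVA or a generalized linear model. Neither statement names a baseline covariate, and neither is called the primary analysis.

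**The concern.** Three things are at stake.

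- **Precision.** A raw change score carries the full noise of the baseline measurement. Regressing the follow-up score on baseline removes the part that baseline predicts. Section 2.6 sizes the trial for 80% power without that gain, so the design has little reserve.
- **Chance imbalance.** With about 29 completers per arm, the arms can differ at baseline by luck. Section 2.2 sets no minimum symptom score for entry, and a patient with few symptoms has little room to improve. Change therefore depends partly on the starting score.
- **The estimand.** Section 2.6 plans for a difference in mean change. If the preliminary check fails, the rank test does not estimate that difference. The switch is foreseeable, because the pilot standard deviations differ (variance ratio 4.36² / 3.15² = 1.92). A rank test also does not cure unequal spread when the aim is to compare locations.

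The second statement in Section 2.7 adds another open choice. Repeated-measures ANOVA with week 0 as one of the response times does not adjust for baseline. A generalized linear model could, but no covariate is stated.

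**Working it through.** **Inputs from Section 2.6:** mean changes 7.21 and 4.35; SDs 4.36 and 3.15; two-sided alpha 0.05; power 0.80; dropout 20%; total 72. Section 2.3 gives 1:1 allocation.

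**Step 1: reproduce the plan's sample size.**
- Difference: 7.21 − 4.35 = 2.86.
- Pooled SD: √((4.36² + 3.15²)/2) = √14.466 = 3.803. Standardised effect: 2.86/3.803 = 0.752.
- Normal approximation: 2 × (1.960 + 0.842)² × 3.803² / 2.86² = 27.8, so 28 per arm. Then 56/0.8 = 70.
- Noncentral t: 29 per arm. Then 58/0.8 = 72.5, so 73.

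The stated 72 lies between the two, so it is sound for an unadjusted comparison of mean change. Expected completers are 72 × 0.8 / 2 = 28.8, about 29 per arm, with power 0.803.

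**Step 2: effect of baseline adjustment.** Let σ² be the variance of the score, assumed equal at week 0 and week 8, and rho the correlation between the two scores. Rho is not in the article, so a range is shown.
- Variance of change: 2σ²(1 − rho).
- ANCOVA residual variance: σ²(1 − rho²).
- Ratio: (1 + rho)/2.

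Power uses the noncentral t at 29 per arm (55 degrees of freedom) with SD 3.803 × √ratio. The extra sample that the unadjusted test would need for the same precision is 1/ratio − 1.

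| Assumed rho | Variance ratio | Power with ANCOVA | Equivalent extra patients without adjustment | Total for 80% power with ANCOVA, incl. 20% dropout |
|---|---|---|---|---|
| 0.3 | 0.65 | 0.937 | 54% | 50 |
| 0.5 | 0.75 | 0.901 | 33% | 55 |
| 0.7 | 0.85 | 0.862 | 18% | 63 |
| 0.9 | 0.95 | 0.823 | 5% | 70 |
| Unadjusted | 1 | 0.803 | – | 73 |

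The gain vanishes as rho approaches 1.

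**Step 3: size of chance imbalance.** The SD of the score implied by the pilot is σ = 3.803/√(2(1 − rho)). A baseline difference of one standard error, σ√(2/29), shifts the change-score difference by (1 − rho)σ√(2/29).
- rho 0.3: 0.7 × 3.214 × 0.2626 = 0.59 points.
- rho 0.5: 0.5 × 3.803 × 0.2626 = 0.50 points.
- rho 0.7: 0.3 × 4.910 × 0.2626 = 0.39 points.

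This is 14% to 21% of the planned 2.86. About one trial in three has an imbalance at least this large. ANCOVA removes the shift.

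**Step 4: does the preliminary test do harm?** The procedure was simulated with 29 per arm, 4,000 runs per scenario, rho 0.3, 0.5 and 0.7, with normal data and with scores rounded and bounded like a sum of six graded items. Under the null, test-then-choose rejected in 0.050 to 0.059 of runs and a fixed t test in 0.049 to 0.060. With a 2.86-point effect and normal data, test-then-choose had power of about 0.80 and ANCOVA 0.94, 0.90 and 0.85. Both arms were generated with the same spread, so these runs do not test the pilot's unequal SDs.

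**The case against.** The strongest reply is that the primary outcome is measured three times and so falls under the repeated-measures statement. On that reading the t or rank test may govern only the outcomes measured at weeks 0 and 8. This stands in part: a reader might infer that the primary outcome will certainly be tested by an unadjusted t or rank test, and the text does not settle that. It does not rescue the plan, because neither route names baseline as a covariate and neither is designated primary.

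A second reply is that covariates are often left to a full protocol or analysis plan, which is not shown and may already contain the adjustment. That is possible. But Section 2.7 does state a between-group test, and the one it states is the less efficient one. Likewise, Section 2.3 mentions only a random number table. That stratification is absent is an inference from silence.

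Third, a comparison of change scores is unbiased under randomization, and with 1:1 allocation a t test tolerates a variance ratio of 1.92 well. A rank test is also defensible for a score built from coarse grades. All of this stands, and it limits the point to efficiency and pre-specification.

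Fourth, a reader might infer that choosing the test on the data inflates false positives. The simulation in step 4 does not support that, and Section 2.3 blinds the analysts to allocation.

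Finally, the size of the gain rests on an assumed rho. For creatinine, cystatin C and eGFR the article gives no correlation, SD or power, so no figure can be claimed. If their correlations are high, the gain is small.

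**Conclusion.** The point holds as a worthwhile improvement. It is not an error in sample size or in type I error: 72 patients give about the planned 80% power for the unadjusted test, and the test-then-choose procedure stayed close to a fixed t test in the scenarios simulated.

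What remains is lost efficiency, exposure to chance baseline imbalance, and a primary estimand that is not fixed in advance. For the primary outcome, adjustment would take power from 0.80 to between about 0.94 (rho 0.3) and 0.82 (rho 0.9).

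These figures assume equal variances at baseline and week 8, about 29 completers per arm, and that the pilot SD describes the week-0 to week-8 change in a total symptom score. Section 2.5 does not define a total, but the pilot mean change of 7.21 exceeds the maximum of 6 for one symptom, so some sum over symptoms is implied.

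**What to change.** In Section 2.7, name one primary analysis: ANCOVA of the week-8 symptom score on arm and week-0 score, or the week-8 contrast of a mixed model with baseline as a covariate. Report the adjusted mean difference with a 95% confidence interval. State that the score is the total over the six symptoms, if that is what is meant.

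If unequal variances are a concern, use robust standard errors with a small-sample correction such as HC3, because uncorrected robust errors can be somewhat liberal at about 29 per arm. Drop the normality and homogeneity check as the switch between tests, and keep the rank test as a sensitivity analysis only. Use the same baseline-adjusted model for the continuous secondary outcomes measured at weeks 0 and 8.

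The baseline values are already collected, so the cost is one degree of freedom and a little analysis work. The sample size need not change. If a separate analysis plan already specifies this model, the two texts only need to be aligned.

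### Two non-equivalent repeated-measures methods are left open for the week 0, 4 and 8 symptom score; one baseline-adjusted mixed model with a week-8 contrast should replace them

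*Protocol article*

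**What the plan says.** All references are to the protocol article.

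- **Outcome measures:** the primary symptom scores are "evaluated at week 0, week 4, and week 8". The secondary laboratory measures are "serum creatinine, cystatin C, and estimated glomerular filtration rate at week 0 and 8". The symptom score is therefore the only efficacy outcome listed with two visits after baseline, and the repeated-measures sentence bears mainly on it.
- **Statistical methods:** the data are to be analysed in SPSS 21.0. A *t* "test, or nonparametric test will be applied for the changes between the 2 groups". The next sentence adds: "Repeated measurement analysis of variance or generalized linear model will be applied for repeated measurement data". No rule chooses between the two methods in that sentence, and none ranks them against the test on changes.
- **Sample size:** the sizing rests on the authors' pilot data, with a mean improvement of 7.21 (SD 4.36) under treatment against 4.35 (SD 3.15) under control. The calculation is two-sided at the 5% level with 80% power. The total allows for losses: "considering a dropout of 20%, 72 patients will be needed totally".

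**The concern.** The word joining the two methods leaves open a choice with consequences. An ordinary generalized linear model has no term for correlation between visits of the same patient. Repeated-measures ANOVA has one, but its SPSS procedure needs a complete set of visits per patient. Depending on the option and the model term reported, the same data could give a test with too many false positives, a test with far too little power, or a complete-case comparison that ignores week-4 scores already collected.

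There is also a question of target. If week 0 enters as one of three repeated levels, the ANOVA group main effect averages over a visit at which randomised groups do not differ in expectation. That average is not the difference in change on which the trial was sized.

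**Working it through.** **Inputs from the article:** mean changes 7.21 and 4.35; SDs 4.36 and 3.15; alpha 0.05 two-sided; power 0.80; dropout 20%; total 72; visits at weeks 0, 4 and 8.

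**Assumptions, not in the article:** an exchangeable within-patient correlation rho of 0.3 to 0.7; the dropout mechanisms in step 4; and that the change used for sizing runs from week 0 to week 8.

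**1. The plan's own figure.** Difference = 7.21 − 4.35 = 2.86. Pooled SD = √((4.36² + 3.15²)/2) = 3.803.
- Normal approximation: 28 per arm; 28/0.8 = 35; 70 in total.
- Noncentral t: 29 per arm; 29/0.8 = 36.25, rounded up to 37; 74 in total (or 58/0.8 = 72.5, so 73, if the total is inflated).

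The stated 72 lies within two patients of 70 and 74 and is reproduced. After 20% loss, 72 × 0.8 = 57.6, so about 57 to 58 completers. At 28 to 29 per arm, power is 0.80 to 0.82 (normal) or 0.79 to 0.80 (t). Restriction to completers is what the sizing already allowed for.

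**2. Generalized linear model with visits taken as independent.**
- *Group effect pooled over k visits.* The true variance is 1 + (k − 1)·rho times the naive one, so alpha = 2·(1 − Φ(1.96/√(1 + (k − 1)·rho))).
- *Week-8-minus-week-0 group contrast.* The naive variance is proportional to 2 and the true one to 2(1 − rho), so alpha = 2·(1 − Φ(1.96/√(1 − rho))). With 29 per arm, SE = 3.803·√(2/29) = 0.999 and 2.86/SE = 2.863. Power = Φ(2.863 − 1.96/√(1 − rho)), against Φ(2.863 − 1.96) = 0.82 for a correct test.

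| rho | alpha, pooled over 3 visits | alpha, pooled over weeks 4 and 8 | alpha, week 8 − week 0 contrast | power of that contrast |
|---|---|---|---|---|
| 0.3 | 0.121 | 0.086 | 0.019 | 0.70 |
| 0.5 | 0.166 | 0.110 | 0.006 | 0.54 |
| 0.7 | 0.206 | 0.133 | 0.0003 | 0.24 |

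The error runs in opposite directions for the two terms.

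**3. Target of the ANOVA group main effect with week 0 as a level.** It estimates (0 + week-4 effect + 2.86)/3. If the week-4 effect is 50% of the week-8 effect, this is (1.43 + 2.86)/3 = 1.43. If it is 75%, this is (2.145 + 2.86)/3 = 1.67. Neither is 2.86. The size of the week-4 effect is an assumption.

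**4. Complete cases under dropout.** A simulation used 36 patients per arm, rho 0.6, about 20% loss after week 4 and 3,000 replicates. Improvement is negative and the true difference is −2.86. Completers' week-8 change was compared by t test. The comparator was a likelihood-type estimate that regresses week 8 on weeks 0 and 4 and averages over all patients.

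| Dropout after week 4 | Completers: estimate under no effect | Completers: type I error | Completers: estimate, true −2.86 | Likelihood-type: estimate, true −2.86 |
|---|---|---|---|---|
| completely random | −0.01 | 0.056 | −2.85 | −2.85 |
| depends on week-4 response, same way in both arms | −0.02 | 0.047 | −2.76 | −2.87 |
| depends on week-4 response, opposite ways by arm | 0.80 | 0.13 | −2.06 (power 0.53) | −2.88 |

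Only the last mechanism does real harm to the complete-case comparison. The likelihood-type estimate stayed close to the truth in all three.

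**The case against.** The strongest reply is that the between-group comparison of changes has its own test, in the sentence before the one at issue. That t or nonparametric test matches the sizing, so the repeated-measures sentence does not by itself govern the primary conclusion. This stands, and it is why the point is not graded higher. It does not settle the matter: the two analyses apply to the same primary score and neither is named as decisive. A test on week-8 change also leaves out patients without a week-8 score.

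A reader might infer several stronger things that the article does not support:

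- *That both methods are wrong.* Repeated-measures ANOVA models the within-patient correlation and is a valid method for three fixed visits. Step 4 shows it has little to answer for under completely random dropout, or under dropout related to response alike in both arms.
- *That completers-only analysis takes power below plan.* The 72 already contains the 20% allowance.
- *That the generalized linear model simply inflates false positives.* That is true of the pooled group effect; the contrast with baseline becomes conservative.
- *That bias from dropout is to be expected.* It needs a mechanism that differs by arm. In a double-blind trial with a matched simulation capsule that is possible, but it is not the natural default.
- *That the article commits to independent visits or to deleting incomplete patients.* It says neither; both follow from the standard form of the named methods. The term may loosely mean SPSS's general linear model or its GEE module.

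Finally, an article may leave the missing-data rule, analysis set and covariance structure to the full plan. Their absence is not held against it here. The point rests on what the sentence states.

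**Conclusion.** The point holds as a should-fix. The sentence offers two methods that behave differently, and one of them, taken at its word, is not valid for several visits per patient. Its true alpha is about 12% to 21% for a group effect pooled over three visits, or 1.9% down to 0.03% for the week-8-minus-week-0 contrast, where power falls from 0.82 to between 0.70 and 0.24. These figures rest on an assumed exchangeable correlation of 0.3 to 0.7.

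The other option is valid under completely random dropout. It wastes week-4 data from patients lost later and is open to bias if dropout depends on response differently by arm. If week 0 is a repeated level, its group main effect does not target the 2.86 used for sizing. The sample size itself is not in question.

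**What to change.** Replace the repeated-measures sentence with one model, and do so before unblinding:

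- **Model:** linear mixed model for repeated measures (SPSS MIXED) on change at weeks 4 and 8, with arm, visit, arm-by-visit, baseline score and baseline-by-visit as fixed effects and an unstructured within-patient covariance.
- **Patients:** all randomised patients with at least one post-baseline score, analysed as randomised.
- **Primary contrast:** the arm difference at week 8.
- **Ranking:** state that the t or nonparametric test on changes is supportive.
- **Single ordinal symptoms:** if a generalized model is wanted, use GEE or a mixed model with patient as the cluster.

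If the full analysis plan already fixes one such model, only the article's wording needs to be aligned with it.

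Cost: slightly more modelling work, and reliance on a missing-at-random assumption, which one sensitivity analysis (for example reference-based or worst-case imputation) can check. The sample size, visits, treatments and software stay as they are.

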## Discussion

3

CKD refers to chronic injury caused by various primary or secondary renal diseases, and it is characterized by insidious and slow progression. In the early stages, there are generally no symptoms or the symptoms vary with different primary diseases. Without proper intervention, it will eventually develop into uremia with the progression and the deterioration of renal function to threaten patients’ life. Therefore, it is important to effectively slow down or even halt the progression of CKD in the early stage.

Compound KA administration could function in renoprotective effect as adjunctive therapy for CKD.^[16]^ Also, it has been reported that BCs could effectively improve the kidney function in patients with nephrotic syndrome and type 2 diabetic nephropathy.^[14,15]^ Although the combination of BC and KA against CKD was rarely reported in high-quality designed trials. In this study, we try to conduct a double-blinded, randomized, controlled trial to observe whether BC combined with KA could alleviate the symptoms of fatigue, anorexia, halitosis, nausea, itching, and edema, improve kidney function in patients with stage 3 CKD. However, there are several limitations in the study. First, it is a single-centered study. Second, the study period may not be long enough to explore whether the combined treatment could delay the CKD progression.
